## Abstract

**Background:**

Benign paroxysmal positional vertigo (BPPV) is the most common cause of vertigo, often effectively treated with standard canalith repositioning maneuvers (CRMs). However, approximately 12.5% of cases remain refractory, leading to persistent symptoms and increased healthcare burden. Variations in the anatomical orientation of the semicircular canals (SCCs) may explain the resistance to conventional maneuvers. This study explores a personalized medicine approach, utilizing computational fluid dynamics (CFD) based on MRI reconstructions to tailor CRMs with the help of mechanical rotation chair according to individual inner ear anatomy.

**Methods:**

We conducted a randomized, multicenter, open-label study targeting patients with refractory posterior canal BPPV. Participants were allocated to either a control group (receiving repeated standard CRMs and Brandt-Daroff exercises) or an intervention group (receiving personalized CRMs based on CFD simulations derived from MRI scans). The intervention group’s maneuvers were executed using a mechanical rotational chair designed for precise angulation. Primary outcomes included resolution of nystagmus and vertigo symptoms, while secondary outcomes measured the reduction in healthcare visits and improved quality of life (Dizziness Handicap Inventory score).

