**Figure 1 fig1:**
[figure not shown]
Visualization and analysis of key anatomical and physical parameters with implications for BPPV treatment. Pressure distribution on the walls of the membranous labyrinth during rotation around the Z-axis for **(a)** real and **(b)** ideally orthogonal semicircular canals. **(c)** Endolymphatic velocities in the posterior semicircular canal obtained during rotation around the Z-axis. A Poiseuille flow with an ampullifugal direction is observed. **(d)** Displacement of otoconia during the standard Epley maneuver. The otoconia exit the posterior semicircular canal but do not reach the utricular macula, indicating that the maneuver cannot be considered successful. Orientation of the horizontal semicircular canal relative to the Frankfurt plane (blue) for **(e)** an idealized model with orthogonal canals, **(f)** the bony labyrinth of the subject shown in the previous figures, and **(g)** the bony labyrinth of a patient refractory to standard treatment. The anomaly in the orientation of the semicircular canals may explain the ineffectiveness of the treatment.

Such models provide valuable insights into the underlying causes of BPPV and help optimize individualized treatment strategies for patients who do not respond to traditional maneuvers (22). For instance, Figures 1e–g highlight the significant deviation of the horizontal semicircular canal in a refractory patient compared to a healthy or idealized model. This anomaly may explain the ineffectiveness of the standard maneuvers for treating BPPV.

If the research hypothesis is correct, adjusting the head movement angles could tailor the repositioning maneuvers to each patient’s specific anatomy. This adaptation could be accurately implemented using a mechanized chair designed for high precision. This approach would enable faster symptom resolution, reduce healthcare costs (in terms of fewer repeated consultations), and shorten the duration of work and functional disability associated with persistent vertigo.

The main objective of the present study is to enhance the effectiveness in treating patients with refractory benign paroxysmal positional vertigo (BPPV) of the posterior semicircular canal through personalized otolith repositioning maneuvers (using a mechanized chair), tailored to the spatial arrangement of each patient’s semicircular canals. This will be compared with the repetition of conventional maneuvers and the use of Brandt-Daroff exercises.

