The secondary objectives are:

To determine whether there are differences at the time of diagnosis (mainly in the characteristics of nystagmus) between patients with refractory BPPV and those who respond well to conventional maneuvers.To develop software capable of generating a mathematical model based on MRI images of the patient’s inner ear, predicting the movement angles necessary to guide the otoliths back to the vestibule. This model will also provide additional information that can be used to rule out or confirm the presence of other underlying pathologies.To quantify the potential reduction in the subjective perception of disability achieved by performing modified, personalized maneuvers compared to the repetition of conventional maneuvers and Brandt-Daroff exercises.To quantify the reduction in healthcare resources (primarily in the number of consultations) achieved through treatment with personalized maneuvers.

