### Randomization process

2.4

*Visit 0 (Randomization visit)*: After obtaining consent, participants will be randomized to one of the following study arms:

Control group: Participants will be advised to perform Brandt-Daroff exercises at home twice daily for 8 weeks. An MRI of the inner ear and posterior cranial fossa will also be requested. If the exercises are ineffective, repositioning maneuvers will be repeated biweekly until symptom resolution using a mechanical rotational chair, specifically the Thomas Richard Vitton (TRV) reposition chair.Study group: Participants will perform Brandt-Daroff exercises at home twice daily for 8 weeks. An MRI will be conducted, and based on the images, a personalized mathematical model will be created to modify the angles of the repositioning maneuver. If the exercises are ineffective, the personalized maneuver will be performed using a mechanized chair.

A balanced block randomization sequence with block size n = 10 will be generated by a member of the research team.

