### Data collection

2.6

Even if intermediate visits are necessary, the following study visits will be conducted according to the protocol (with data recording):

Visit 1 (eight weeks after inclusion):

The Dix-Hallpike Test (DHT) will be performed with videonystagmographic recording. If positive:In the control group, the conventional Epley maneuver will be repeated using a mechanized chair.In the study group, a personalized Epley maneuver will be performed using a mechanized chair.

Visit 2 (ten weeks after inclusion):

The DHT will be repeated with videonystagmographic recording. If positive:In the control group, the conventional Epley maneuver will be repeated using a mechanized chair.In the study group, the personalized Epley maneuver will be repeated using a mechanized chair.These maneuvers (conventional for the control group and personalized for the study group) will be repeated every two weeks until resolution of symptoms (or up to a maximum of 8 repetitions).

Visit 3 (Six months after inclusion):

The following variables will be recorded:Dix-Hallpike Test (DHT) results (negative or positive).Dizziness Handicap Inventory (DHI) score.Number of consultations required for resolution.

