### Sample size and calculation methodology

2.10

To estimate the sample size, we assume that approximately 25% of patients with refractory BPPVp may be cured through repeated maneuvers or Brandt-Daroff exercises (control group). A significant difference of 50% in the study group (i.e., a 75% efficacy rate for symptom resolution) is considered clinically meaningful. With a 95% confidence level (1-*α*) and 95% statistical power for a two-tailed hypothesis test, a sample size of 23 participants per arm is required. Thus, the estimated total sample size is 46 individuals, increased to 54 (27 per group) to account for a 15% anticipated dropout rate.

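### The abstract and objectives make Brandt-Daroff exercises part of the comparator and name the chair for the personalized side, but both arms get both; the trial compares maneuver angles only.

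*Protocol article*

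**What the plan says.** Four places put Brandt-Daroff on the control side.

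- Abstract, Methods: participants go to "a control group (receiving repeated standard CRMs and Brandt-Daroff exercises) or an intervention group (receiving personalized CRMs", the latter based on simulation. The chair is then mentioned for one arm: "The intervention group’s maneuvers were executed using a mechanical rotational chair designed for precise angulation".
- Introduction, main objective: the aim is better treatment "through personalized otolith repositioning maneuvers (using a mechanized chair), tailored to the spatial arrangement of each patient’s semicircular canals". The comparator follows: "This will be compared with the repetition of conventional maneuvers and the use of Brandt-Daroff exercises".
- Introduction, third secondary objective (perceived disability): "personalized maneuvers compared to the repetition of conventional maneuvers and Brandt-Daroff exercises".
- Section 2.10: the 25% rate is for patients who "may be cured through repeated maneuvers or Brandt-Daroff exercises (control group").

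The operational sections describe something else.

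- Section 2.4: "Study group: Participants will perform Brandt-Daroff exercises at home twice daily for 8 weeks". The control group is advised to do the same exercises at the same frequency for the same eight weeks. In each arm, chair maneuvers follow only if the exercises have not worked.
- Section 2.6: at eight and ten weeks, if the Dix-Hallpike test is positive, "In the control group, the conventional Epley maneuver will be repeated using a mechanized chair". The study group has its personalized Epley in a mechanized chair under the same condition.
- Section 2.9 confirms that the exercise period comes before the personalized maneuver.

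**The concern.** The objective determines what the trial will be said to have shown. Read with the abstract, it describes a comparison of personalized chair maneuvers with a package of conventional maneuvers and Brandt-Daroff. A positive result could then be reported as superiority over Brandt-Daroff, or over maneuvers performed without a chair. Under 2.4 and 2.6, neither the exercises nor the chair differ between the arms, so randomization says nothing about either.

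The chair matters in its own right. The Discussion treats chair versus manual maneuvers as a separate question and reports earlier work in which the chair did not significantly outperform manual treatment. A reader of the abstract would reasonably take the chair to be part of the randomized contrast.

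The same ambiguity reaches 2.10, where cures by Brandt-Daroff are labelled as a control-group event although the study group does the exercises too.

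**Working it through.** **1. The arms side by side**

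| Component | Control: abstract and objectives | Study: abstract and objectives | Control: 2.4 and 2.6 | Study: 2.4 and 2.6 |
|---|---|---|---|---|
| Brandt-Daroff, 8 weeks | named | not named | yes (2.4) | yes (2.4; also 2.9) |
| Mechanized chair | not named | named (abstract, main objective) | yes (2.4, 2.6) | yes (2.4, 2.6) |
| Maneuver angles | conventional | personalized | conventional | personalized |
| Who receives a maneuver | not stated | not stated | those still positive at week 8 | those still positive at week 8 |

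In the last two columns only the angles differ. Section 2.6 bears on the chair; it does not mention Brandt-Daroff, which comes from 2.4 and 2.9.

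**2. The stated sample size**

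Inputs from 2.10: p1 = 0.25, p2 = 0.75, two-sided alpha 0.05, power 95%. With pooled variance under the null and no continuity correction, and mean rate 0.50:

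n = [1.960 × √(2 × 0.50 × 0.50) + 1.645 × √(0.25 × 0.75 + 0.75 × 0.25)]² / 0.50²
= [1.386 + 1.007]² / 0.25 = 22.9, so 23 per arm.

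Power at 23 per arm is 95.1%. The plan's figure reproduces.

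**3. What the two rates could mean**

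Section 2.8 follows intention to treat, so a participant cured by the exercises counts as a success in either arm. Let b be the share cured by the exercises in both arms. The document gives no value, so those below are assumed.

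*Whole-arm reading.* If 25% and 75% already include exercise cures, 23 per arm and 95% power stand. The rates among those who go on to a maneuver are then (0.25 − b)/(1 − b) and (0.75 − b)/(1 − b):

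| b (assumed) | Control maneuver | Personalized maneuver |
|---|---|---|
| 10% | 16.7% | 72.2% |
| 20% | 6.3% | 68.8% |
| 25% | 0% | 66.7% |

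*Maneuver-only reading.* If 25% and 75% are rates among those who receive a maneuver, the whole-arm rates are b + (1 − b) × 0.25 and b + (1 − b) × 0.75, and the difference shrinks to 0.50 × (1 − b):

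| b (assumed) | Control | Study | Power at 23 per arm |
|---|---|---|---|
| 10% | 32.5% | 77.5% | 89.3% |
| 20% | 40.0% | 80.0% | 81.2% |
| 30% | 47.5% | 82.5% | 71.5% |

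**4. Which reading the text favours**

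The 25% in 2.10 covers cure by maneuvers or by Brandt-Daroff, so exercise cures are already in it. The 75% is that rate plus 50 points. The whole-arm reading is therefore the natural one, and the last table illustrates only the alternative. Its upper end also fits poorly with the Introduction, which counts Brandt-Daroff among methods of low efficacy.

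**The case against.** The best defence is that the operational sections agree with one another and define a coherent randomized comparison: Brandt-Daroff and then conventional chair maneuvers, against Brandt-Daroff and then personalized chair maneuvers. The control group does receive what the abstract and objective list. Neither text says that the study group goes without the exercises or that controls are treated manually; they simply do not mention it. The abstract's Discussion presents the expected benefit as coming from optimized angles, which is what is randomized.

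Most of this stands. A reader might infer that the trial cannot answer its question at all, and that would go too far, because the angle comparison is valid. A reader might also infer that the trial is underpowered. The document does not support that either: the loss requires the maneuver-only reading, which 2.10 disfavours, and an exercise cure share that is stated nowhere. Nor does anything suggest that a null result would be presented as equivalence to Brandt-Daroff; no such claim is planned.

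The defence does not remove the mismatch. Condensing an abstract can explain an omission there. It does not explain a main objective and a secondary objective that both name Brandt-Daroff on the comparator side, or a sample-size premise that labels exercise cures as control-group cures.

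**Conclusion.** The point holds as an inconsistency in the stated contrast that limits what may be concluded. Taking 2.4 and 2.6 as the conduct of the trial, the randomized treatment difference is personalized versus conventional angles, both in the chair, after Brandt-Daroff in both arms, and it operates only in participants still positive at week 8. A positive result would support that claim. It would not show superiority over Brandt-Daroff or over maneuvers done without the chair.

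No error in the sample size is shown: 23 per arm gives 95% power on the whole-arm reading. Only if 25% and 75% were meant as rates among those receiving a maneuver would the stated power be too high, by an amount that depends on an exercise cure share the document does not give. Which description of the arms is the intended one is for the sponsor to settle.

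**What to change.** Reconcile the abstract, the main objective and the third secondary objective with 2.4 and 2.6. If 2.4 and 2.6 describe the trial as run, state the objective as personalized versus conventional maneuver angles, both in the mechanized chair, after eight weeks of Brandt-Daroff in both arms, and limit the planned conclusion to that.

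In 2.10, remove the implication that exercise cures occur only in the control group, and state that 25% and 75% are whole-arm rates including exercise cures in both arms. If they were instead meant as rates among those who receive a maneuver, say so, give the assumed exercise cure share with its basis, and restate the power.

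The cost is text edits and a narrower claim. On the whole-arm reading, neither conduct nor sample size changes.

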**Discussion:**

Personalized CRMs based on CFD models may enhance treatment efficacy for refractory BPPV by optimizing maneuver angles according to the specific SCC orientation. This approach could significantly reduce symptom persistence, decrease the need for repeated healthcare visits, and improve patient outcomes. The use of non-invasive MRI and CFD techniques represents a novel step toward individualized treatment in vestibular disorders, with potential for broader application in personalized otoneurology. Further analysis will determine the extent of clinical benefit and cost-effectiveness of this approach.

**Clinical trial registration:**

ClinicalTrials.gov, Identifier: NCT06725966.

## Introduction

1

Vertigo is a common symptom in the general population, significantly limiting the ability of affected individuals to perform many activities, even the most basic daily tasks (1). The most frequent cause of vertigo is benign paroxysmal positional vertigo (BPPV) (2), with an estimated incidence ranging from 10 to 140 per 100,000 people and a lifetime prevalence of 2.4% (3, 4).

BPPV is caused by the displacement of otoliths, which normally adhere to the maculae of the utricle and saccule. When these otoliths detach, they float freely in the endolymph of the posterior labyrinth and often enter one of the semicircular canals, most frequently the posterior canal (4), followed by the horizontal and superior canals. In most cases, the otoliths move freely within the canal (canalithiasis), shifting under the influence of gravity when the patient changes the position of their head. This movement generates an endolymphatic current that stimulates sensory cells in the ampulla, resulting in nystagmus and a subjective sensation of vertigo. These patients experience recurrent episodes of brief vertigo (less than one minute), typically triggered by head movements such as lying down, sitting up, turning in bed, bending forward, or looking upward.

Occasionally, otoliths may adhere to the cupula (cupulolithiasis) rather than moving freely in the canal. The clinical effect is similar to that of canalithiasis: certain head movements cause deflections in the ampulla, where increased density due to the adhered otoliths leads to repeated vertigo episodes.

Diagnosis is achieved through provocation maneuvers (5, 6), where specific head positions cause otolith movement in the semicircular canals, resulting in vertigo and nystagmus. The characteristics of the nystagmus (mainly its direction) help determine which canal is affected, and in the case of the horizontal canal, whether it involves canalithiasis (geotropic nystagmus) or cupulolithiasis (ageotropic nystagmus). The main diagnostic maneuvers include the Dix-Hallpike test (7), McClure test, and head extension. Although diagnosis can be made through direct observation of nystagmus with the naked eye or using amplification systems like Frenzel glasses, videonystagmography is ideal as it allows for quantifying nystagmus intensity and duration as well as determining its direction.

Treatment, similar to diagnosis, involves maneuvers aimed at repositioning the otoliths back into the vestibule, expelling them from the semicircular canals. Specific maneuvers are available for each canal: Epley (8) and Semont (9) for the posterior canal, Lempert (10) and Gufoni for the horizontal canal, and Yacovino (11) or reverse Epley for the superior canal. The effectiveness of these maneuvers is high, with resolution rates around 90% for the most commonly affected canal (the posterior canal). Traditionally, these maneuvers are performed manually on a treatment table, although this method does not guarantee precise angulation of movements. Recently, a mechanized chair has become available, allowing precise execution of each maneuver and facilitating treatment in patients with mobility issues (e.g., obesity or cervical spine stiffness).

Despite the high success rate of these maneuvers, a significant number of patients [estimated at 12.5% of BPPV diagnoses (12)] do not achieve resolution of symptoms. These cases result in repeated healthcare visits, prolonged periods of work disability, and significant family burden, turning an otherwise benign and easily treatable condition into a persistent medical, social, and occupational problem.

Various strategies have been proposed for the treatment of refractory BPPV. These include habituation exercises [such as Brandt-Daroff maneuvers (13), aimed at dispersing the otoliths], transtympanic corticosteroid instillation (14) before performing maneuvers (attempting to reduce potential edema in the membranous labyrinth that may prevent otolith movement toward the vestibule during repositioning), and even surgical interventions (e.g., canal plugging or sectioning of the singular nerve). However, none of these approaches have definitively resolved the issue, either due to the low efficacy of certain methods (e.g., Brandt-Daroff maneuvers or corticosteroid instillation) or the significant side effects associated with surgical interventions (e.g., hearing loss and intracranial complications).

One plausible explanation for the ineffectiveness of maneuvers in certain patients may be individual variations in the spatial arrangement of the semicircular canals. Typically, the canals form angles of approximately 90° relative to one another, and repositioning maneuvers are designed based on this anatomical assumption. However, it is well known that there are individual differences in the angles between these structures (15), potentially resulting in a mismatch between the patient’s anatomy and the movements used in standard maneuvers. A mathematical model indicating the exact anatomical arrangement of the semicircular canals and predicting the expected movement of otoliths would allow the maneuver to be tailored to the specific anatomy of each patient, essentially enabling personalized medicine.

For patients with refractory BPPV, imaging (specifically, magnetic resonance imaging of the posterior cranial fossa) is recommended to rule out a neurological cause (16). This MRI typically includes the internal ears of the patient. From a routine clinical MRI of the inner ear, a personalized mathematical model can be developed. This process involves several stages and has been successfully applied in the development of personalized therapies in other fields, such as Cardiology. Initially, the digital version of the MRI is used to create a 3D model representing the endolymphatic fluid container. From this, a mathematical model based on Navier–Stokes equations is developed and solved using Computational Fluid Dynamics (CFD) techniques.

CFD-based numerical simulations offer a non-invasive tool for analyzing the human vestibular system, capable of predicting experimentally observed behaviors. For example, they can estimate the transcupular pressure threshold below which the membranous labyrinth’s response ceases to be linear, known as the mechanical adaptation effect (17). This innovative approach provides insights into understanding various vestibular pathologies, such as the Tullio phenomenon (18) and Ménière’s disease (19).

Through numerical simulation and CFD analysis of a high-resolution micro-CT as described in previous work (20), we previously conducted a study to evaluate vestibular stimulation on the crista ampullaris during rotations mimicking the Head Impulse Test (HIT) (21). Instead, for this clinical study, we focused primarily on the pressures on the labyrinth walls and velocities of the endolymph when combined with a particle model representing the otoliths. Examples of the results obtained from these simulations are shown in Figures 1a–d.

